### Shoulder and neck function tests

AROM of the shoulders and neck will be performed in the patients’ group with a low skeletal muscle mass before and 6 months after TL according to a standardized protocol. The flexion, abduction, rotation, extension and flexion of the shoulder and neck and forward flexion and abduction the shoulder will be examined using a goniometer. The mean of two sequential measurements will be used for further analysis [43].

### Patients’ experienced need for neck and shoulder rehabilitation

Qualitative research will be performed by semi-structured interviews to get insight in the patients’ experiences with and insights in the treatment and its morbidity, such as the effects on shoulder and neck function, related to provided information and therapy. Data will be analyzed with a thematic analysis approach [44]. This part of the study will be performed and written according to the Standards for Reporting Qualitative Research (SRQR) [45]. Participants will be recruited until saturation will be achieved, which is when no new information will be identified from the last two interviews and expected to occur between six and twelve interviews [46, 47].

The semi-structured interviews will be conducted using pre-defined topic guides. This topic guide is open to changes when interviews identify new information. All participants will be asked about possible shoulder and neck function problems, how this is handled by the patient and whether rehabilitation was required.

### Swallowing function

Function tests on the swallowing quality of the TL-patients with low SMM will be assessed by the performance of videofluoroscopy (VFSS). Patients will be offered thin liquid (thinned Micropaque), thick liquid (Micropaque purely) and firm consistency (toast in Micropaque) in 3 steps. Each step will be performed twice.

### Voice quality

The quality of the voice of patients with low SMM will be measured by the performance for voice recording and the associated Acoustic Voice Quality Index (AVQI) [48, 49]. AVQI is a multi-parameter model in which the outcomes of six acoustic parameters are measured and combined into one objective measure of the voice quality.

### Other parameters

Patients’ demographic, staging, treatment and outcome data will be collected using electronic patient records. To allow for comparison with the recent Dutch Head and Neck Society audit the same characteristics and potential predictive factors will be evaluated [4]. The following parameters will be added: peroperative data (i.e. type of closure of the neopharynx), comorbidity scores (ACE-27 and Charlson Comorbidity Index), American Society of Anesthesiologist’s physical status (ASA score), WHO performance status and preoperative laboratory results, which will be analyzed from routine blood tests. General postoperative complications (except from PCF-rate) are graded according to the Clavien-Dindo classification of Surgical Complications [50]. Severe complications are defined as Clavien-Dindo grade 3 A or higher [41–44].

### Cost-effectiveness analysis

A detailed analyses of cost and effect differences for patients having a PMMF and standard of care (no PMMF) will be assessed using a health care perspective. All healthcare consumption for every individual patient will be collected from electronic patient files. Subsequently units of health care consumption will be linked to respective Dutch unit costs according to available lists of the Dutch Health Care Institute. The economic evaluation will take place both via a trial based approach and making use of decision analytical modeling to extrapolate outcomes. Uncertainty of outcomes will be depicted by both deterministic as well as probabilistic sensitivity analyses.

### Power calculation

Subtraction of data from the meta-analyses from Paleri et al. [13] and Sayles et al. [12] revealed that the PCF rate for patients with and without PMMC or PMMF for reinforcement is reduced (11/114 (0.10) to 47/156 (0.30)), giving a relative risk of 0.32. After exclusion of the patients who received a reconstruction of the pharynx from the database of Bril et al. [18], the PCF rate in patients with low SMM was 31.0%. Assuming that the same relative risk as in the meta-analyses is applicable, this leads to our hypothesis that a prophylactic PMMF can reduce the PCF rate from 31.0 to 9.9%.

To show that the use of PMMF can reduce the fistula rate for TL patients with low SMM, 61 patients per arm are needed (two sided alpha 0.05 and power 85%). With an expected drop-out of 5%, a total of 128 patients with low SMM are needed. This power calculation was performed with the program PASS (two-sided Z-test with pooled variance). Since approximately 46% of TL patients has low SMM, a total of about 276 TL patients are required to include 128 patients with low skeletal muscle mass.

### Statistical analysis

Our primary hypothesis is that the use of PMMF as onlay for reinforcement can reduce the PCF rate in patients with low SMM after TL from 31.0 to 9.9%. To test this hypothesis, we will compare the incidence of fistula formation in patients with low SMM between the group with PMMF (intervention arm) and the group without PMMF lap (control arm) by the Chi-squared test or when needed the Fisher’s exact test (N < 5). To demonstrate the association between SMM and fistula formation, the incidence of fistula formation in the control arm (low SMM without PMMF) will be compared with the incidence of fistula formation in the (non-randomized) group of normal SMM. The relative risk will be calculated with an associated 95% confidence interval. Modified Poisson regression models will be used to correct for potential confounder, such as radiotherapy in prehistory, type of closure of the neopharynx etc.

Results of our other outcomes will be presented as the mean scores with standard deviation for continuous variables or as median with interquartile range for ordinal or non-normal distributed continuous data. Differences between groups with or without PMMF will be tested by independent t-tests for normally distributed continuous data and for ordinal and non-normal distributed continuous data Mann Witney U tests will be used. Differences over time within groups with or without PMMF will be tested by paired t-tests for normally distributed continuous data and for ordinal and non-normal distributed continuous data Wilcoxon signed-rank tests will be used.

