Several risk factors for PCF have been described in literature such as prior chemoradiotherapy, the extent of the pharyngectomy, neck dissection, pre-treatment tracheostomy, preoperative albumin and low BMI [3, 4, 17, 18]. A nationwide Dutch study showed a broad range of PCF incidence between the centers of the Dutch Head and Neck Society (NWHHT), which could not be fully explained by the prediction model developed with known risk factors know at that time. More recently also, a preoperative radiological assessed low skeletal muscle mass (SMM) was found to be an independent risk factor for PCF development [18, 19].

In recent years, research on body composition and especially on SMM has increased. It appears that a low SMM is associated with acute and late adverse events in patients with head and neck cancer during (chemo)radiotherapy [20–23], flap-related complications [24, 25], decreased survival rates [26–29], and PCF [18, 19]. This emphasizes the importance of considering SMM in assessing PCF risk.

Therefore, in this randomized controlled trial (RCT), our primary aim is to investigate if the use of PMMF as onlay on the pharyngeal closure for reinforcement will reduce the PCF rate in TL patients with a high risk for PCF because of low SMM.

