**Fig. 2 Fig2:**
[figure not shown]
Timeline of including patients

After informed consent, patients with low SMM will be centrally randomized between prophylactic PMMF at the time of TL or not. A stratified permuted-block procedure randomizes patients to the groups on a 1:1 ratio. Strata include treating center and concomitant neck dissection. Both primary and secondary outcome measurements as described below will be evaluated in the group with low SMM.

Patients without low SMM will undergo the TL as regularly scheduled, will not be randomized and only the primary outcome measurement will be evaluated.

Patients definitively scheduled for TL with reconstruction of the pharynx using the PMMC meet the exclusion criteria and thus will not be recruited for the study. If in an included patient, regardless of SMM and possible randomization, it is unexpectedly decided peroperatively that a PMMC is required for reconstruction of the pharynx, these patients will be followed over time. The primary outcome measurement will still be evaluated.

In conclusion, the primary outcome measure is thus evaluated in the following groups:

Patients with a low SMM who will undergo a TL with PMMF.Patients with a low SMM who will undergo a TL without PMMF.Patients without a low SMM who will undergo TL as regularly scheduled.Patients who unexpectedly need a PMMC for reconstruction of the pharynx during the TL, regardless of their SMM.

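### The primary chi-squared test ignores the randomisation strata: conservative and slightly less powerful if centre effects are strong, little different if they are not

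*Protocol article*

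**What the plan says.** **Randomisation** (Study design and population). Patients with low skeletal muscle mass are allocated 1:1 by stratified permuted blocks: "Strata include treating center and concomitant neck dissection".

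**Prognosis** (Introduction). Neck dissection appears in the list of fistula risk factors. On centre: "A nationwide Dutch study showed a broad range of PCF incidence between the centers of the Dutch Head and Neck Society", and the known risk factors did not fully explain that range.

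**Primary test** (Statistical analysis). The flap arm is compared with "the group without PMMF lap (control arm) by the Chi-squared test", or with Fisher's exact test under a condition given only as N < 5. A relative risk with a 95% interval is planned. Modified Poisson models are added to correct for confounders. Their open-ended list names earlier radiotherapy and type of closure; neither stratification factor is named, and the model is not the primary test.

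**Sample size** (Power calculation). The hypothesis is that "a prophylactic PMMF can reduce the PCF rate from 31.0 to 9.9"%, with "two sided alpha 0.05 and power 85"%, so that "61 patients per arm are needed". The calculation used an unstratified test: "This power calculation was performed with the program PASS (two-sided Z-test with pooled variance").

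**The concern.** Stratified blocks force the arms to be nearly balanced on centre and neck dissection. If those factors predict fistula, the arm difference varies less from trial to trial than under simple randomisation. A crude test still charges the between-stratum variation to error, so its standard error is too large.

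The trial expects few events: 61 × 0.310 = 18.9 in the control arm and 61 × 0.099 = 6.0 in the flap arm, about 25 in all. Precision that the design has already paid for is then worth using. The protocol fixes the primary test by name, so this concerns what is stated and not a detail left open.

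The Fisher condition is a related wording gap. It does not say whether N is an observed or an expected cell count.

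**Working it through.** **1. The plan's own figure.** Inputs from Power calculation: 31.0% v 9.9%, two-sided 5%, power 85%.

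- Unpooled formula: n = (1.960 + 1.036)² × (0.310 × 0.690 + 0.099 × 0.901) / 0.211² = 61.1 per arm.
- The closed-form pooled formula gives 65 per arm, or 83.2% power at 61.
- Exact enumeration of the pooled Z-test at 61 per arm gives 84.7%.
- Drop-out: 122 / 0.95 = 128.4, against the stated 128.

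So 61 per arm gives about 85% with the crude test. The square of the pooled Z statistic is the Pearson chi-squared statistic, so the planned test matches the sizing basis.

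**2. Why the crude test is conservative.** With stratum weights w_k and rates p_k,

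p̄(1 − p̄) = Σ w_k p_k(1 − p_k) + Σ w_k (p_k − p̄)².

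The crude test uses the whole left side. With near-perfect balance within strata, only the first term on the right drives the arm difference. If the second term is a share R of the total, the size is about 2Φ(−1.96/√(1 − R)). For illustration, R = 5% gives 2Φ(−2.011) = 4.4%, and R = 15% gives 2Φ(−2.126) = 3.4%. R is not known here.

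**3. Simulation.** From the protocol: 122 patients, 1:1 blocks within centre × neck dissection, 31.0% v 9.9% (31.0% in both arms under the null). Assumed: blocks of 4, 10 or 11 centres of equal expected size, half the patients with neck dissection, normally distributed centre effects on the log-odds scale (SD) and an odds ratio (OR) for neck dissection. There were 12,000 runs per setting with 10 centres and 8,000 with 11. Monte Carlo standard error is about 0.2 points for size and 0.3–0.4 for power. The Cochran-Mantel-Haenszel (CMH) statistic is [Σ(a_k − n_1k m_k/n_k)]² / Σ[n_1k n_0k m_k(n_k − m_k) / (n_k²(n_k − 1))], where a_k is flap-arm events and m_k all events in stratum k.

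To show what each SD means, the third column gives the 10th–90th percentile of centre rates around the 26% national rate in the Introduction.

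| Centres | SD, OR | Centre rates | Size %, crude v CMH | Power %, crude v CMH |
|---|---|---|---|---|
| 10 | 0, 1 | all 26% | 4.9 v 4.8 | 84.4 v 83.1 |
| 10 | 0.5, 1.5 | 15–39% | 4.5 v 4.8 | 84.8 v 84.4 |
| 10 | 0.75, 1.5 | 11–45% | 4.4 v 5.3 | 85.7 v 86.0 |
| 10 | 1.0, 2 | 7–51% | 3.6 v 4.9 | 86.0 v 87.6 |
| 11 | 1.0, 2 | 7–51% | 2.9 v 4.4 | 84.7 v 86.8 |
| 11 | 1.5, 2 | wider still | 2.9 v 5.3 | 85.5 v 89.8 |

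With 11 centres and no stratum effect, power was 84.5% v 83.0%. Across the settings run, coverage of the crude 95% interval for the relative risk rose under the null from about 95.5% (no stratum effect) to 97–98% (strong effects). At the design effect it was 96–97% throughout.

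**4. Sparse strata.** Eleven centres × 2 gives 22 strata, or 122 / 22 = 5.5 patients each. In simulations of this kind, 25–38% of patients fell in strata that add nothing to CMH, and at least one centre had no events in 67–94% of trials.

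**5. The N < 5 condition.** With 61 per arm at the planned rates:

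- Observed count below 5: P(Bin(61, 0.099) ≤ 4) = 26.6%. The control arm adds practically nothing.
- Expected count below 5: the average is 61 × (0.310 + 0.099)/2 = 12.5, and the chance of falling below 5 is about 0.004%.
- The reading can decide the result: 4 v 12 fistulas gives p = 0.032 by chi-squared and 0.058 by Fisher. On average the observed-count switch costs little (power 84.7% to 84.4%).

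**The case against.** The strongest reply is that nothing planned is lost. The crude test is the one the trial was sized on, and its power stays at about 84–86% in every row above. The stratified test offers a possible gain, not the repair of a shortfall. That stands.

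The size of the gain also depends on a quantity the protocol does not give. The wide range between centres is reported for laryngectomy patients in general. This comparison takes only low-muscle-mass patients and excludes chemoradiotherapy for an earlier head and neck carcinoma and planned flap, gastric or jejunal reconstruction, so some of the case mix behind that range may be gone. That stands too, and it is why the conclusion is conditional.

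A reader might infer more than the documents support:

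- **That the p-value is invalid or false positives are inflated.** The departure is only in the conservative direction, so a significant crude result remains valid.
- **That the confidence interval is generally wrong.** Over-coverage that grows with the stratum effects appears under the null, not at the design effect.
- **That a switch to Fisher's test is likely.** The usual meaning of such a rule is expected counts, under which it almost never applies. The 27% belongs to the other reading.

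The open-ended covariate list could include the strata, but in a secondary model. It does not change the named primary test.

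**Conclusion.** The mismatch between design and primary analysis is plain in the text, and the protocol itself links both strata to fistula. Its consequence is modest and conditional.

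- **Strong centre effects** (SD about 1 or more on the log-odds scale): crude size about 3–4% and about 1–4 points of power forgone.
- **Weak to moderate effects:** little or no difference.
- **No stratum effect:** CMH on fully crossed strata loses about 1 point (1.3 and about 1.5 in the two runs shown).

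These figures rest on assumed centre numbers, centre sizes, block length and effect sizes. This is a recommendation on efficiency and on consistency with the design. It is not a flaw that threatens validity or the sample size.

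**What to change.** Make the primary comparison account for the randomisation strata. One suitable form is a Cochran-Mantel-Haenszel test with a Mantel-Haenszel relative risk and 95% interval, stratified by neck dissection and centre. Pooling of small centres is essential because many crossed strata will be sparse. Fix the pooling rule before analysis and base it on enrolment, not outcome.

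A modified Poisson model with arm, neck dissection and pooled centre is an alternative. It is not equivalent to CMH on crossed strata, and unpooled centres without events would leave its centre terms inestimable.

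Keep the crude chi-squared test as supportive. If a Fisher fallback is kept there, say that N < 5 means expected counts.

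The cost is a change of analysis wording, with no new patients or data, since each patient's stratum is known at randomisation. The downside is the possible loss of about 1 point of power if the strata turn out not to be prognostic; fewer, pooled strata should reduce it.

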#### Secondary outcome measurements

In low SMM patients shoulder and neck function, swallowing function, and voice quality with their consequences on quality of life (QoL) will be investigated by questionnaires before and 6 months after TL.

The following questionnaires will be assessed:

Quality of life: European Organization for Research and Treatment for Cancer Quality of Life Questionnaires, EORTC QLQ-C30, EORTC-QLQ-H&N35, and EuroQol 5D 5 L (EQ-5D-5 L) [33–35].Shoulder and neck function: the Shoulder Disability Questionnaire (SDQ) [36], Shoulder Pain and Disability Index Dutch Language Version (SPADI-DLV) [37] and the Neck Disability Index (NDI) [38].Swallowing function and dysphagia: The Dysphagia Severity Scale (DSS) and Dysphagia Quality of Life Scale (DQOL), after laryngectomy the Swallow Outcomes After Laryngectomy (SOAL) [39], the M.D. Anderson Dysphagia Inventory (MDADI) [40] and the Functional Oral Intake Scale (FOIS) for dysphagia (the only investigator reported outcome measurement (IROM)) [41].Voice quality: Voice Handicap Index (VHI) [42].

Shoulder and neck function tests will be performed depending on the feasibility in the participating center also before and 6 months after TL. In addition, this latter group of patients will be recruited 3 months after TL to have a voice recording and a video fluoroscopy (VFSS). Performance of these side studies will also be performed on the available logistics of the participating center.

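### Quality-of-life and function outcomes have a baseline, but the planned between-arm tests do not adjust for it and the within-arm paired tests do not estimate the PMMF effect

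*Protocol article*

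**What the plan says.** Protocol article, Secondary outcome measurements: quality of life, shoulder and neck function, swallowing and voice "will be investigated by questionnaires before and 6 months after TL". The section on shoulder and neck function tests sets the same two time points for active range of motion (AROM). Three outcomes have no stated baseline: SOAL is given after laryngectomy, and the voice recording (AVQI) and videofluoroscopy (VFSS) take place at 3 months.

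Protocol article, Statistical analysis, on these outcomes:

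- Between arms: "Differences between groups with or without PMMF will be tested by independent t-tests for normally distributed continuous data", with Mann-Whitney tests for ordinal or non-normal data.
- Within arms: "Differences over time within groups with or without PMMF will be tested by paired t-tests for normally distributed continuous data", with Wilcoxon signed-rank tests otherwise.

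The only regression model in that section, the modified Poisson model, stands in the paragraph on fistula. Under Study design and population, randomisation is stratified by centre and concomitant neck dissection. The tests named for the secondary outcomes use neither factor.

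**The concern.** The secondary objective is a comparison of the two arms. Two features of the stated methods serve it poorly.

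First, a pre-operative value is collected, but no method named for these outcomes adjusts the arm comparison for it. Precision matters because these are largely the possible harms of the flap. The Discussion wants shoulder morbidity, dysphagia and voice loss weighed against fewer fistulas, and the trial is sized only for fistula.

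Second, a paired test inside one arm measures TL and flap together, or TL alone. Because TL may change voice, swallowing and neck scores in both arms, neither result isolates the flap. The Discussion presents within-patient and between-patient comparisons together as showing what the flap does to these functions. That makes it easy to set one arm's p-value against the other's.

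**Working it through.** **The plan's own figure.** The article gives no sample size for the secondary outcomes. For fistula it states that "61 patients per arm are needed" (31.0% against 9.9%, two-sided 0.05, 85% power). The unpooled normal formula gives (1.960 + 1.036)² × (0.31×0.69 + 0.099×0.901) / 0.211² = 61.1. The pooled normal formula gives 65. Exact binomial enumeration of the pooled Z-test at 61 per arm gives 84.7% power. For drop-out, 122/0.95 = 128.4, against the stated 128. The figure of 61 is therefore reproduced closely enough to use below as the number per arm at 6 months.

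**Inputs**

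- n = 61 per arm (Power calculation, after 5% drop-out). This is an upper figure for AROM, which depends on feasibility at each centre.
- Correlation r between baseline and 6 months: not in the documents; assumed 0.3 to 0.7.
- True arm difference: not in the documents; assumed 0.5 SD or 0.4 SD. The SD is taken as equal at both time points.

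**Variance of the arm difference**, relative to a test on the 6-month score:

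- 6-month score: 1
- change score: 2(1 − r)
- baseline-adjusted (ANCOVA): 1 − r²

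The ratio of ANCOVA to change score is (1 − r²) / [2(1 − r)] = (1 + r)/2.

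**Power** = Φ( d / √(2v/n) − 1.96 ), with v the factor above. For d = 0.5 and v = 1: 0.5/√(2/61) = 2.76; 2.76 − 1.96 = 0.80; power 78.9%.

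| r | 6-month score: v, power | Change score: v, power | Baseline-adjusted: v, power | Variance cut vs 6-month score | Variance cut vs change score |
|---|---|---|---|---|---|
| 0.3 | 1, 78.9% | 1.40, 64.6% | 0.91, 82.5% | 9% | 35% |
| 0.5 | 1, 78.9% | 1.00, 78.9% | 0.75, 89.0% | 25% | 25% |
| 0.7 | 1, 78.9% | 0.60, 94.6% | 0.51, 97.2% | 49% | 15% |

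For d = 0.4, the 6-month-score test has 59.8% power. Adjustment gives 63.9%, 72.3% and 87.1% at r = 0.3, 0.5 and 0.7. The difference detectable at 80% power falls from 0.507 SD to 0.484, 0.439 and 0.362 SD.

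Which unadjusted test is better depends on r, with the crossing at 0.5. The adjusted analysis is better than both at each value of r in the table.

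**Within-arm tests.** Suppose the arms do not differ, and let p be the chance that one arm's paired test is significant. The chance that exactly one of the two arms reaches significance is 2p(1 − p). If neither arm changes, this is 2 × 0.05 × 0.95 = 9.5%. If both arms change by 0.25 SD with r = 0.5, then p = 0.485 and it is 2 × 0.485 × 0.515 = 50.0%. A simulation of 20,000 trials gave 50.2%, while the between-arm t-test on the 6-month score rejected in 5.0%.

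**The case against.** The strongest reply is that nothing planned is invalid. The unadjusted between-arm test holds its level, as the simulation shows, and it is listed before the paired tests. The paired tests can be read as answering a separate question, how patients change over time. This stands: the loss is one of precision, on secondary outcomes.

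A reader might infer that the baseline is discarded altogether. The text does not support that. It does not say which quantity is compared, and a change-score test would use the baseline, though inefficiently.

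A reader might also infer that the trial will judge the flap by contrasting within-arm p-values. The article nowhere says so, so the 50% figure shows the risk of a misuse and is not the error rate of a planned analysis.

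The gain may also be small. TL alters the anatomy between the two measurements, so for voice and swallowing r could be low. At 0.3, adjustment removes only 9% of the variance of a 6-month-score test. Quoting only the 25% to 49% that holds at r of 0.5 to 0.7 would show the favourable end.

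The absence of an interval for these outcomes is not a fault in itself, since an article may leave reporting detail to the full protocol or analysis plan. Finally, linear ANCOVA does not suit every scale, and centre may be too sparse as a covariate where function tests are done only in some hospitals. Both points are accepted and shape the fix.

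**Conclusion.** The point holds as a matter of efficiency and of what the tests can answer. For outcomes with a baseline, the article specifies a valid but less precise arm comparison and adds within-arm tests that do not estimate the PMMF effect. Under the assumed correlations of 0.3 to 0.7, adjustment removes 9% to 49% of the variance if the planned test uses the 6-month score. If it uses change, the saving runs from 35% at r = 0.3 to 15% at r = 0.7.

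The correlation, the effect size and the equal SDs are assumptions, and 61 per arm is the most that can be expected for AROM. Adjustment does not make the trial powered for harm: even at r = 0.7 the detectable difference is 0.36 SD, so a non-significant result would still not show absence of harm. The fistula analysis and its sample size are not affected.

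**What to change.** Replace the two sentences on between-group and within-group tests with the following:

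- **Outcomes with a baseline:** compare 6-month values between arms in a model with arm, baseline value and neck dissection, plus centre. Pool small centres or fit centre as a random effect.
- **Type of model:** ANCOVA for approximately continuous scores; an ordinal or rank-based model with baseline adjustment for clearly ordinal scales such as FOIS.
- **Reporting:** the adjusted between-arm difference with its 95% CI.
- **Within-arm change:** descriptive only, with no paired tests.
- **Outcomes without a stated baseline (SOAL, VFSS, AVQI):** the same model without the baseline term, at their own time point.

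Naming the 6-month value as the response also settles which quantity is compared. The cost is analysis wording, fixed before the data are examined, with no new measurements. A rule for missing baselines is needed, mainly for AROM, where baseline testing depends on the centre.
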